## Abstract

**Background:**

In parallel to the traditional symptomatology, deficits in cognition (memory, attention, reasoning, social functioning) contribute significantly to disability and suffering in individuals with schizophrenia. Cognitive deficits have been closely linked to alterations in early auditory processes (EAP) that occur in auditory cortical areas. Preliminary evidence indicates that cognitive deficits in schizophrenia can be improved with a reliable and safe non-invasive brain stimulation technique called tDCS (transcranial direct current stimulation). However, a significant proportion of patients derive no cognitive benefits after tDCS treatment. Furthermore, the neurobiological mechanisms of cognitive changes after tDCS have been poorly explored in trials and are thus still unclear.

**Method:**

The study is designed as a randomized, double-blind, 2-arm parallel-group, sham-controlled, multicenter trial. Sixty participants with recent-onset schizophrenia and cognitive impairment will be randomly allocated to receive either active (*n*=30) or sham (*n*=30) tDCS (20-min, 2-mA, 10 sessions during 5 consecutive weekdays). The anode will be placed over the left dorsolateral prefrontal cortex and the cathode over the left auditory cortex. Cognition, tolerance, symptoms, general outcome and EAP (measured with EEG and multimodal MRI) will be assessed prior to tDCS (baseline), after the 10 sessions, and at 1- and 3-month follow-up. The primary outcome will be the number of responders, defined as participants demonstrating a cognitive improvement ≥*Z*=0.5 from baseline on the MATRICS Consensus Cognitive Battery total score at 1-month follow-up. Additionally, we will measure how differences in EAP modulate individual cognitive benefits from active tDCS and whether there are changes in EAP measures in responders after active tDCS.

**Discussion:**

Besides proposing a new fronto-temporal tDCS protocol by targeting the auditory cortical areas, we aim to conduct a randomized controlled trial (RCT) with follow-up assessments up to 3 months. In addition, this study will allow identifying and assessing the value of a wide range of neurobiological EAP measures for predicting and explaining cognitive deficit improvement after tDCS. The results of this trial will constitute a step toward the use of tDCS as a therapeutic tool for the treatment of cognitive impairment in recent-onset schizophrenia.

**Trial registration:**

ClinicalTrials.gov NCT05440955. Prospectively registered on July 1^st^, 2022.

**Supplementary Information:**

The online version contains supplementary material available at 10.1186/s13063-023-07160-z.

## Administrative information

Note: the numbers in curly brackets in this protocol refer to SPIRIT checklist item numbers. The order of the items has been modified to group similar items (see http://www.equator-network.org/reporting-guidelines/spirit-2013-statement-defining-standard-protocol-items-for-clinical-trials/).

**Table Taba:** 

Title {1}	Efficacy and auditory biomarker analysis of fronto-temporal transcranial direct current stimulation (tDCS) in cognitive impairment associated with recent-onset schizophrenia: study protocol for a multicenter randomized double-blind sham-controlled trial *Short title:* tDCS for Cognitive Impairment Associated With Recent-onset Schizophrenia (STICOG) *Original French title:* Efficacité et tolérance de la stimulation électrique transcrânienne fronto-temporale gauche à courant continu (tDCS) comme traitement du déficit cognitif chez les sujets atteints de schizophrénie débutante : un essai multicentrique, randomisé, contrôlé.
Trial registration {2a and 2b}	Clinicaltrials.gov registration number: NCT05440955, first posted on July 1^st^, 2022
Protocol version {3}	version 0.2 on June 7^th^ 15th, 2021, substantial modification n°1
Funding {4}	The French Ministry of Health, DGOS, PHRC IR Interrégional 2020

## Introduction

### Background and rationale {6a}

Schizophrenia is a chronic psychiatric disorder that affects around 1% of the population worldwide. The disorder is recognized as the 8th leading cause of handicap in young adults by the World Health Organization [1]. Life expectancy is reduced by 10–20 years of age, as a consequence of the increased prevalence of non-psychiatric comorbidities, substance abuse, and suicide rates in this population [2]. Schizophrenia has also a profound effect on the patient’s environment, as demonstrated by high levels of subjective burden on relatives of diagnosed individuals [3, 4].

Schizophrenia results from an interaction between vulnerability genes and environmental risk factors. This interaction alters brain development and triggers the clinical manifestations of the disorder in early adulthood. The diagnosis is made primarily on the basis of symptoms, including positive (delusions/hallucinations), negative (flattened affect/avolition), and disorganization (disorganized thoughts/odd behavior) symptoms, associated with reduced psychosocial functioning. At present, treatment mainly consists of antipsychotic medications combined with psychosocial interventions [1]. Treatment-resistance remains an enduring feature for 20–60% of patients [5, 6], which stresses the need to develop further therapeutic approaches.

In parallel to the traditional symptomatology, deficits in cognition (i.e., memory, attention, reasoning, social functioning) contribute significantly to disability and suffering in individuals with schizophrenia. Cognitive deficits have been closely linked to alterations in early auditory processing (EAP) that occur in auditory cortical areas [7–9]. Mechanistically, alterations in EAP have been demonstrated to lead to poor functional outcomes associated with impaired cognition in patients [10–12]. At the molecular level, EAP deficits involve impairments at both cortical and subcortical stages of processing, particularly involving GABAergic, glutamatergic, and N-methyl-D-aspartate receptor (NMDAR)-mediated processes [13]. EAP deficits can be traced using multimodal behavioral and neural measures of EAP, including behavioral tone-matching performance [8], functional neuroimaging of the auditory cortex [14], and early auditory event-related potentials [15, 16] which could thereby serve as surrogate endpoints in procognitive intervention studies in schizophrenia.

Preliminary evidence indicates that cognitive deficits in schizophrenia can be improved with a reliable and safe non-invasive brain stimulation technique called tDCS (transcranial direct current stimulation). tDCS consists of the application of a direct electrical current through two electrodes placed on the scalp to modulate cortical activity. Applied repeatedly over the left frontal and temporal cortices, tDCS significantly improves cognitive performance such as memory and attention in patients with schizophrenia [17, 18]. In parallel to the cognitive improvement, a large amount of randomized sham-controlled studies have reported promising beneficial effects and safety of fronto-temporal tDCS on core clinical manifestations of the disorder such as hallucination and negative symptoms [19–21]. We have further suggested the use of tDCS as a safe first-line agent to both improve the clinical and cognitive manifestations of at-risk mental state and prevent the onset of frank psychosis [22].

Trials are needed to verify the results of cognitive improvements after tDCS in larger schizophrenia cohorts with adequate sham control and randomization. In that sense, additional tDCS trials in schizophrenia are ongoing and receive important funding from governments and foundations across the world [23, 24]. Despite these promising aspects, two areas of uncertainty warrant additional attention. First, meta-analyses of phase III trials indicate that a significant proportion of patients derive no cognitive benefits after tDCS treatment [25, 26]. Second, the neurobiological mechanisms of cognitive changes after tDCS have been poorly explored in trials and are thus still unclear, which hinders the advance of neurostimulation approaches for schizophrenia. There is therefore a critical necessity to develop biomarkers that can help predict which subset of patients will or will not benefit from tDCS, and help determine the biological underpinnings of tDCS-induced cognitive changes.

### Objectives {7}

#### Objective 1 (main objective) and hypothesis

Objective 1 is to compare the efficacy of a left fronto-temporal active tDCS treatment (10 sessions of 20 min delivered over 5 consecutive weekdays) versus sham on global cognitive impairment in patients with recent-onset schizophrenia, at 1-month follow-up. At 1-month we will assess the number of responders, defined as patients demonstrating a cognitive improvement greater than or equal to *Z*=0.5 from baseline on the MATRICS Consensus Cognitive Battery total score (MCCB, a standardized test battery to assess cognitive functions in patients with schizophrenia [27–29].

We hypothesize that there will be significantly more responders in the active group.

#### Secondary objectives and hypotheses

##### Objective 2: clinical efficacy

Objective 2a is to compare the long-term efficacy of active tDCS versus sham on global cognitive impairment in patients with recent-onset schizophrenia at 3-month follow-up.Objective 2b is to compare the efficacy of active tDCS versus sham on different cognitive aspects (processing speed, attention/vigilance, working memory, verbal learning, visual learning, problem-solving, emotional awareness) measured with the MCCB in patients with recent-onset schizophrenia at 1- and 3-month follow-up.Objective 2c is to compare the efficacy of active tDCS versus sham on different clinical aspects of schizophrenia (hallucinations, positive, negative, disorganization, depression, grandiosity/excitement, manic symptoms, and subjective experience of cognitive impairment) measured with validated symptom rating scales in patients with recent-onset schizophrenia at the end of the tDCS treatment and at 1- and 3-month follow-up.Objective 2d is to compare the efficacy of active tDCS versus sham on the outcome (functioning, quality of life) measured with validated rating scales in patients with recent-onset schizophrenia at the end of the tDCS treatment and at 1- and 3-month follow-up.

We hypothesize that subjects randomly allocated to the active group will demonstrate better improvement from baseline cognitive, symptoms, and functional scores than subjects randomly allocated to the sham group.

##### Objective 3: tolerance

Objective 3 is to compare the clinical tolerance of active tDCS versus sham measured with adverse effects questionnaires in patients with recent-onset schizophrenia at the end of the tDCS treatment.

We hypothesize that subjects randomly allocated to the active group will demonstrate no significant difference in questionnaire scores than subjects randomly allocated to the sham group.

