### Criteria for discontinuing or modifying allocated interventions {11b}

Modification of the allocated intervention for a given participant (active tDCS or sham tDCS) based upon any reasons will not be allowed. In case of tDCS treatment discontinuation, the participant will be withdrawn from the study.

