##### Secondary outcome 3: tolerance

Outcome 3 is the score after the last tDCS session in the following tolerance measures:tDCS-AEQ (adverse effects questionnaire) [42]VAMS (visual analog mood scale) [43].

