## Statistical methods

### Statistical analysis plan

In general, the normality of the data distributions will be investigated with Shapiro-Wilk tests. Between-group comparisons will be performed with Mann-Whitney *z*-tests and two-sample *t*-tests for non-normal and normal continuous outcomes, respectively. Categorical data will be compared with chi-square tests. Both intention-to-treat and per-protocol analyses will be conducted. In case of significant interactions, post hoc analyses will be conducted using appropriate contrasts. Analyses will be adjusted or stratified by the study site as part of a sensitivity analysis. The significance threshold will be set at *P*-value < 0.05 and appropriate effect sizes of significant results will be calculated.

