##### Secondary outcome 3: tolerance

Outcome 3: tDCS tolerance questionnaire scores measured after tDCS will be compared between the active tDCS and sham tDCS groups using mean comparison tests.

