### Methods in analysis to handle protocol non-adherence and any statistical methods to handle missing data {20c}

Protocol non-adherence will be described as follows: characteristics at inclusion, arm (active tDCS or sham tDCS), withdrawal date and visit number, reason for withdrawing, and last outcomes carried forward. For the trial (*N*=60), the analyses will be conducted on the intention-to-treat set, including all randomized participants with at least one assessment conducted after the tDCS treatment (10 sessions). Per protocol analyses will be performed using the whole sample (*N*=60). The last observation carried forward will be used for missing data.

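### Objective 3 treats a non-significant difference among treatment completers as its tolerance result, with no margin and no planned effect size, so it cannot support equal tolerance

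*Protocol article*

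**What the plan says.** All references are to the protocol article.

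- **Objective 3: tolerance** sets the hypothesis: patients on active stimulation "will demonstrate no significant difference in questionnaire scores than subjects randomly allocated to the sham group".
- **Outcomes {12}, Secondary outcome 3** fixes the timing: "Outcome 3 is the score after the last tDCS session in the following tolerance measures", namely the tDCS-AEQ and the VAMS.
- **Statistical methods {20a}, Secondary outcome 3** fixes the test: the scores "will be compared between the active tDCS and sham tDCS groups using mean comparison tests". No margin is attached there or elsewhere, and Trial design {8} declares a superiority trial.
- **Criteria for discontinuing {11b}**: "In case of tDCS treatment discontinuation, the participant will be withdrawn from the study".
- **Section {20c}** defines the intention-to-treat set as "including all randomized participants with at least one assessment conducted after the tDCS treatment (10 sessions"), and adds: "The last observation carried forward will be used for missing data".
- **Statistical analysis plan** ends with the rule that "appropriate effect sizes of significant results will be calculated".

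**The concern.** A hypothesis of no significant difference counts as met whenever p exceeds 0.05. That happens when tolerance is similar, and also when the sample is small or the scores are noisy. Loss of participants makes the hypothesis easier to meet.

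Two other rules compound this. First, the score exists only for those who reach the last session, so anyone who stops because stimulation was badly tolerated is outside the comparison. If such stopping is commoner under active stimulation, the comparison is tilted in favour of active tDCS. Second, the result that the objective predicts is the one for which no effect size is planned.

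At stake is a secondary but safety-relevant statement. A report following the plan could present the tolerance hypothesis as confirmed when active stimulation is moderately worse tolerated, without showing how large a difference the data leave open.

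**Working it through.** **Inputs.** From the document: 30 per arm, threshold 0.05, response rates 33% and 5%, power 80%. Assumed: two-sided testing (the sidedness is not stated), equal SDs, and a t-test. Mann-Whitney is planned if the scores are not normal, which would shift the figures somewhat. The document gives no SD or margin for the questionnaires, so differences are in SD units. It gives no dropout rate either; 20% is used as an illustration.

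**The plan's own figure.** Sample size {14}, two-sided, pooled variance, no continuity correction, mean rate (0.33 + 0.05)/2 = 0.19:

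n = [1.96·√(2·0.19·0.81) + 0.84·√(0.33·0.67 + 0.05·0.95)]² / 0.28² ≈ 29.6, so 30 per arm and 60 in total. The stated figure reproduces. It concerns the responder outcome; nothing is sized for tolerance.

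**Precision for tolerance at 30 per arm.**

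- Standard error of the difference: √(2/30) = 0.258 SD.
- 95% half-width: t(0.975; 58 df) × 0.258 = 2.00 × 0.258 = 0.52 SD.
- Difference detectable with 80% power: about 0.74 SD (noncentral t; 0.72 by normal approximation).

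**Chance of a non-significant result when active is truly worse** (noncentral t, noncentrality d/√(2/n)):

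| True excess burden | 30 per arm | 24 per arm (20% loss, assumed) |
|---|---|---|
| 0.3 SD | 1 − 0.208 = 79% | 1 − 0.174 = 83% |
| 0.5 SD | 1 − 0.478 = 52% | 1 − 0.396 = 60% |

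**What a margin would need.** With a true difference of zero, one-sided 2.5% and 80% power, n per arm = 2·[(1.96 + 0.84)/margin]². This is 63 for a margin of 0.5 SD and 175 for 0.3 SD. At 30 per arm only a margin of about 0.72 SD or wider reaches 80% power, so a formal non-inferiority claim is out of reach for any tighter margin.

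**Who is in the comparison.** Take a participant who stops at session 3 because of adverse effects. Section {11b} withdraws them. They then have no assessment after the ten sessions, so {20c} leaves them out of the intention-to-treat set. Carrying the last observation forward does not bring them back: they are outside the set, and the text of Outcome 3 defines no earlier questionnaire score to carry. The comparison is therefore in effect one of completers. The size of any resulting bias cannot be computed, because no discontinuation rate is given.

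**Effect sizes.** The hypothesized result for Objective 3 is non-significance, and the stated rule covers significant results. The expected outcome thus has no planned effect size.

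**The case against.** The fair case against has four parts.

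1. **No passage says that equal tolerance will be concluded.** The objective is to compare, and the sentence at issue is a prediction. That is correct. But the prediction is the stated hypothesis, and non-significance is what would confirm it.

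2. **The trial's safety evidence does not rest on two questionnaires.** Section {22} records every adverse event, with causality and follow-up to resolution; {30} sets three months of adverse-reaction evaluation; {21a} has an independent committee review safety at least yearly; and {20c} already describes withdrawals by arm, date and reason. This stands. A reader might infer that tolerance as a whole is unsupported, and the document does not bear that out. What lacks support is equality inferred from Outcome 3.

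3. **The effect-size sentence does not exclude other estimates.** It contains no word such as only, responder percentages are compared in both arms whatever the p-value, and mixed models yield estimates in any case. A reader might infer that published efficacy effects will be materially inflated by selection on significance. That would require non-significant estimates to be withheld, which the document does not say. Even then, at its own 33% against 5%, exact enumeration of the uncorrected chi-square test at 30 per arm gives a mean difference among significant results of 30.6 points against a true 28, about 1.09-fold. Larger inflation needs response rates that the protocol does not state.

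4. **Treatment lasts five weekdays, so few may stop.** Possibly; the document gives no rate. The power figures assume all 30 per arm are analysed and do not measure the effect of leaving out those who stop.

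**Conclusion.** The point holds for the tolerance comparison. As written, Objective 3 can be met when active stimulation is worse tolerated by 0.3 SD (79% of the time) or 0.5 SD (52%), and a non-significant result leaves an interval of about ±0.52 SD around the estimate. Discontinuation, outcome timing and the analysis set together confine the score to completers; the direction of any bias depends on which arm loses more intolerant participants, and its size is unknown. The effect-size rule plans nothing for the result that is expected. The figures rest on two-sided 0.05, equal SDs, a t-test and full data on 30 per arm; losses make them worse.

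It does not extend to the trial's safety monitoring, which is separate, or to a claim of inflated efficacy results. It should be corrected, but it concerns a secondary objective and leaves the primary analysis untouched.

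**What to change.** - **Objective 3 and Outcome 3:** state the aim as estimating the active-minus-sham difference in tDCS-AEQ and VAMS scores with a 95% confidence interval, and say that p > 0.05 will not be read as equal tolerance.
- **Outcome 3 timing and set:** use the last available questionnaire score for every participant who received any stimulation, with the form completed at the last session attended. This concerns data collection only and leaves the rule on stopping stimulation as it is; {11b} and {20c} should be worded so that these scores are kept and analysed.
- **Reporting:** present the withdrawal description already planned in {20c}, by arm and reason, next to the tolerance result.
- **Statistical analysis plan:** replace the restriction to significant results with effect sizes for all primary and secondary outcomes, with 95% confidence intervals, whatever the p-value.

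The cost is wording, plus one operational change. Since the last session attended is often known only afterwards, the short form may have to be filled in at each session. No extra patients are needed.

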##### Objective 4: response markers and predictors

Objective 4a is to assess how differences in EAP mechanisms modulate individual cognitive benefits from active tDCS measured with a range of EAP measures in patients with recent-onset schizophrenia at 1-month follow-up.Objective 4b is to evaluate whether there are changes in EAP measures in patients associated with cognitive improvement after active tDCS at 1-month follow-up.

We hypothesize that baseline EAP measures will distinguish between participants who have improved cognitive deficits after active tDCS and those who do not, and that changes in EAP measures after tDCS will be only observed in participants with improved cognitive deficits after active tDCS.

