### Trial design {8}

The present study is designed as a superiority, double-blind, parallel-group, sham-controlled randomized clinical trial with an allocation ratio of 1:1. Study sites will include 4 University Hospital centers in France. In a 1 × 2 factorial design with sham, patients are randomized into two groups: active tDCS and sham tDCS. A total of 60 patients with schizophrenia will be randomly assigned to receive either active tDCS (*N*=30) or sham tDCS (*N*=30). Psychiatric and neuropsychological assessments will be performed at baseline (time of consent), at the end of the tDCS procedure, and at 1 and 3 months following the end of the tDCS procedure (maintenance effect). Auditory biomarker analyses will involve neurobiological measures (multimodal magnetic resonance imaging and neurophysiology) recorded at baseline and at 1 month after tDCS. Study schedule and study flowchart are presented in Figs. 1 and 2.

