##### Secondary outcome 4: response markers and predictors

Outcome 4a is the differences at baseline in the following EAP measures between patients with cognitive improvement and patients without cognitive improvement after active tDCS:Correlations (*z*-scores) between left prefrontal and temporal cortical areas (i.e., areas stimulated with tDCS) measured with resting-state functional magnetic resonance imaging (MRI).Spectral power (dB) and inter-assay coherence (%) in gamma frequency (40-Hz) during specific auditory paradigms (auditory steady-state, oddball, tone-matching) measured with electroencephalography (EEG).GABA and glutamate levels (mM) within left prefrontal and temporal cortical areas measured with resting-state Magnetic Resonance Spectroscopy (MRS)radiotracer binding potential on GABA-A receptors (Binding Potential) within left prefrontal and temporal cortical areas measured with resting-state [^11^C]flumazenil positron emission tomography MRI (PET-MRI).

Outcome 4b is the changes between baseline and 1-month follow-up in the same EAP measures in patients with cognitive improvement compared to patients without cognitive improvement after active tDCS.

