### Sample size {14}

Based on previous tDCS studies in patients with schizophrenia (rev. in [17], we assume that a third (33%) of participants in the active tDCS group and 5% of participants in the sham tDCS group will be responders (improvement greater than or equal to *Z*=0.5 from baseline on the MCCB total score). Based on this estimated difference, we calculated that 60 patients are required to demonstrate a difference between the two groups with a power of 80% (*p* = 0.05).

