##### Secondary outcome 4: response markers and predictors

Outcome 4a: the difference at baseline between responders and non-responders in EAP measures will be analyzed using mixed effects regression models with cognitive improvement status (responder or non-responder) and group (active or sham) as independent variables.Outcome 4b: the changes from baseline to 1-month follow-up in EAP measures will be analyzed using mixed effects regression models with cognitive improvement status (responder or non-responder), group (active or sham), and time (before tDCS and 1-month follow-up) as independent variables.

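### The Objective 4 hypothesis predicts auditory-marker change only in active-tDCS responders, but the planned analysis can show larger change in responders, not absence of change in everyone else

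*Protocol article*

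**What the plan says.** All places are in the Protocol article. Under Objective 4 (response markers and predictors), the objective is worded as one of association: "Objective 4b is to evaluate whether there are changes in EAP measures in patients associated with cognitive improvement after active tDCS at 1-month follow-up". The hypothesis sentence that follows goes further and predicts that "changes in EAP measures after tDCS will be only observed in participants with improved cognitive deficits after active tDCS".

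Under Outcomes, outcome 4b is a comparison of EAP change "in patients with cognitive improvement compared to patients without cognitive improvement after active tDCS". Under Statistical methods for primary and secondary outcomes, "the changes from baseline to 1-month follow-up in EAP measures will be analyzed using mixed effects regression models with cognitive improvement status", treatment group and time as independent variables. The general Statistical analysis plan section adds: "In case of significant interactions, post hoc analyses will be conducted using appropriate contrasts". It sets the threshold at P < 0.05 and provides for effect sizes of significant results only.

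The sample size section covers the primary outcome alone, assuming that "a third (33%) of participants in the active tDCS group and 5% of participants in the sham tDCS group will be responders".

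**The concern.** The word 'only' makes the hypothesis two statements: EAP measures change in active responders, and they do not change in active non-responders or under sham. The second is a claim of no effect. A significant interaction says that changes differ between subgroups; it does not say that the change in any one of them is zero. A non-significant contrast in a small subgroup does not say so either.

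The Discussion intends the EAP measures to help predict and explain cognitive improvement and expects the results to guide selection of participants for later tDCS trials. A report that EAP changed only in those who improved would be taken as evidence that EAP change is specific to benefit. That pattern can arise when non-responders also change, simply because their change is estimated too imprecisely to reach significance. Because effect sizes are planned for significant results only, the estimate that would reveal this has no stated place in the report.

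**Working it through.** **Inputs from the protocol.** 30 patients per arm; assumed responder rates 33% (active) and 5% (sham); threshold P < 0.05. Sidedness is not stated, so two-sided is assumed.

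**Inputs not in the protocol.** The EAP effect size, its SD and the correlation between baseline and 1 month. Effects below are therefore assumptions, in SD of the change score, shown over a range.

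**1. The protocol's own figure.** For 33% versus 5%, two-sided 0.05, 80% power, pooled variance, no continuity correction:

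n = [1.960·√(2·0.19·0.81) + 0.842·√(0.33·0.67 + 0.05·0.95)]² / 0.28² = (1.087 + 0.436)² / 0.0784 ≈ 29.6, so 30 per arm and 60 in total. The stated 60 reproduces. It is for the primary outcome; no figure is given for 4b.

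**2. Subgroup sizes.** Active responders 0.33 × 30 = 9.9, about 10; active non-responders 0.67 × 30 = 20.1, about 20; sham non-responders 0.95 × 30 = 28.5, taken as 28.

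**3. Chance of missing a true within-subgroup change.** Paired t-test, noncentral t with n − 1 degrees of freedom and noncentrality δ√n. For n = 20, √n = 4.472 and the critical value is 2.093.

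| True change (SD of change) | δ√n, n = 20 | Missed, 20 active non-responders | Missed, 28 sham non-responders |
|---|---|---|---|
| 0.3 | 1.342 | 75% | 67% |
| 0.5 | 2.236 | 44% | 28% |
| 0.8 | 3.578 | 8% | 2% |

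If 0.5 SD is meant on the raw score, δ = 0.5/√(2(1 − ρ)), and the miss rate at n = 20 is 57%, 44%, 22% and 8% for correlations ρ of 0.3, 0.5, 0.7 and 0.8. A one-sided test at 0.5 SD of change misses 31%.

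**4. Precision.** The 95% CI half-width at n = 20 is 2.093/4.472 = 0.47 SD of change. A non-significant result is compatible with a true change approaching 0.9 SD.

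**5. Does requiring a significant interaction first help?** Simulation of t-tests on change scores, 10 active responders and 20 active non-responders, SD 1 (400,000 runs per row). The gate is a significant responder versus non-responder difference in change. The false pattern is a significant change in responders with a non-significant one in non-responders.

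| True change, responders / non-responders | Gate opens | False pattern, no gate | False pattern and gate open | Non-responder contrast non-significant, given gate open |
|---|---|---|---|---|
| 0.5 / 0.5 | 5% | 13% | 2% | – |
| 1.0 / 0.5 | 24% | 35% | 16% | 68% |
| 1.0 / 0.3 | 42% | 60% | 36% | 89% |

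So the gate largely removes the false pattern when both subgroups change equally. It does not do so when responders change more but non-responders also change: among trials that pass the gate, the non-responder change usually fails to reach significance.

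**The case against.** The other side has four good points.

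- **'Only' is in the hypothesis, not in the objective or outcome 4b.** This stands. The objective asks about association and outcome 4b is already a comparison of improvers with non-improvers, so the hypothesis sentence is what is out of line.
- **A reader might infer that the 4b conclusion is planned to rest on a non-significant test in about 20 non-responders.** The protocol does not say that. It plans a mixed model with status, group and time, and nowhere states that a non-significant contrast will be read as no change. What can be said is that no planned test would support 'only'.
- **A reader might also take 13% as the false-pattern rate when both subgroups change equally.** That holds only without the gate. The protocol runs contrasts after significant interactions, and if the relevant one is responder status by time the rate is about 2%. The protocol does not say which interaction opens the contrasts, so both figures are needed.
- **The 44% is a single point on an assumed effect size, from a paired t-test standing in for the mixed model.** This stands too, which is why the range from 75% to 8% is given.

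Finally, equivalence margins and detailed reporting rules for biomarkers may properly sit in an analysis plan that is not shown. Their absence is not part of this point. The point concerns what the protocol does state: a hypothesis of absence, and effect sizes limited to significant results.

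**Conclusion.** The concern holds in a limited form. The Objective 4 hypothesis claims more than the planned model and contrasts can establish: they can support larger EAP change in active responders, not absence of change in active non-responders or sham.

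The size depends on an assumed effect. If the non-responder change is truly 0.8 SD it will seldom be missed; at 0.3 to 0.5 SD it will be missed often, including after a significant interaction. These figures assume the planned responder rates, complete EAP data, two-sided testing and t-tests on change scores.

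Severity is minor. The objective is secondary, and neither the primary outcome nor trial conduct is affected.

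**What to change.** 1. In the Objective 4 hypothesis, replace the prediction that change occurs only in active responders with one that change is larger in them. This matches outcome 4b as already defined.
2. Base the 4b conclusion on the difference in EAP change, active responders minus active non-responders, with its 95% CI.
3. In the Statistical analysis plan section, extend effect-size reporting so that the EAP change with its 95% CI in active non-responders and in sham is given whatever the P-value.
4. State that absence of change will not be concluded from a non-significant contrast.

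The cost is a few sentences of wording, with no new data, visits or patients. The downside is that the trial will usually be unable to claim that EAP changed only in responders. The difference itself will also be imprecise: with about 10 versus 20 patients, power is about 24% for a difference of 0.5 SD of change and 70% for 1.0 SD.
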